## Abstract

**Background:**

The SARS-CoV-2 outbreak has resulted in a tremendous increase in hospital and intensive care unit (ICU) admissions all over the world. Patients with severe coronavirus disease 2019 (COVID-19) warranting ICU treatment usually have prolonged mechanical ventilation and are expected to be prone to develop psychological impairments, such as post-traumatic stress disorder (PTSD), anxiety and depression, which negatively impact quality of life. To date, no effective treatment strategy is available. In the current trial, we aim to assess the effect of an ICU-specific virtual reality (ICU-VR) intervention on psychological well-being and quality of life after COVID-19 ICU treatment.

**Methods:**

In this multicentre, randomized controlled trial, we aim to examine whether COVID-19-specific ICU-VR, offered 3 months after hospital discharge, improves psychological well-being and quality of life. Secondary objectives are, firstly, to examine the intra-group changes in psychological well-being and quality of life and the inter-group differences in psychological well-being and quality of life during follow-up, up to 12 months after hospital discharge, and secondly, to examine patients’ satisfaction with and rating of ICU care and aftercare and patients’ perspectives on ICU-VR. Eighty adult patients treated for COVID-19 in the mixed-surgical ICUs of four hospitals in Rotterdam, the Netherlands, will be included and randomized (1:1) to either early or late ICU-VR between June 29 and December 31, 2020. Patients randomized to early ICU-VR will receive the ICU-VR intervention during an outpatient clinic visit 3 months after hospital discharge, whereas patients randomized to late ICU-VR will receive ICU-VR 6 months after hospital discharge. Primary outcomes of this study are psychological well-being, assessed using the Impact of Event Scale–Revised (IES-R) and the Hospital Anxiety and Depression Scale (HADS), and quality of life, assessed using the European Quality of Life 5 Dimensions (EQ-5D) and RAND-36 questionnaires, up to 6 months after hospital discharge.

**Discussion:**

Currently, an effective treatment for psychological sequelae after ICU treatment for specific illnesses is unavailable. Results from this study will provide insight whether virtual reality is a modality that can be used in ICU aftercare to improve psychological well-being and quality of life, or satisfaction, after ICU treatment for specific illnesses such as COVID-19.

**Trial registration:**

This trial has been retrospectively registered on the Netherlands Trial Register on August 14, 2020 (NL8835).

**Supplementary Information:**

The online version contains supplementary material available at 10.1186/s13063-021-05271-z.

## Administrative information

Note: The numbers in curly brackets in this protocol refer to SPIRIT checklist item numbers. The order of the items has been modified to group similar items (see http://www.equator-network.org/reporting-guidelines/spirit-2013-statement-defining-standard-protocol-items-for-clinical-trials/).

Role of sponsor {5c}	Neither the sponsor, nor the funding sources, had any role in the study design; collection, management, analysis, and interpretation of data; writing the manuscript of the protocol, or the decision to submit the protocol for publication. They will not have any authority over any of these activities.

## Introduction

### Background and rationale {6a}

The SARS-CoV-2 pandemic in December 2019 has resulted in a tremendous increase in hospital and intensive care unit (ICU) admissions [1–4]. While initial reports from China indicated that approximately 5% of patients with SARS-CoV-2 were admitted to the ICU, reports from Italy suggest that this number may be as high as 16%, leading to stressed ICU capacity [5, 6].

Critically ill patients with severe pulmonary disease treated in the ICU are known to develop long-term impairments [7–10]. These impairments consist of psychological, physical and cognitive impairments and are collectively referred to as the post-intensive care syndrome (PICS) [11–14]. The psychological component of PICS consists of post-traumatic stress disorder (PTSD), anxiety and depression, is the most important determinant of a decreased health-related quality of life and negatively impacts a patients’ ability to rehabilitate [8, 15–17].

Prevention and treatment of PICS is a major objective to achieve a sustained improvement in the quality of ICU care in the decades to come. Despite growing awareness, several interventions aiming to improve psychological well-being have yielded unsatisfactory and ambiguous results [18–22]. Psychological sequelae after ICU exposure are hypothesized to reflect a combination of sensory overload and delusional memories [23–25]. Veracious reconstruction of memories to fill in memory gaps and reframe delusional memories may reduce these psychological symptoms [26].

Virtual reality (VR) is a relatively new technique that has been proven to be effective for treating several psychological impairments, including PTSD and anxiety disorders [27–30]. VR has three major advances: first, it represents a means of addressing the limitations of imaginal exposure and overcomes a significant hurdle of imaginal exposure, the inability to engage in sufficient detail, and affective magnitude to recreate the traumatic event; second, it is an appropriate tool for patient information delivery; and third, using VR, one can truthfully reconstruct phases of ICU treatment to replace and adjust possible delusional memories, the largest contributor to psychological distress [26, 31].

ICU-specific VR (ICU-VR) is safe and immersive and improves psychological well-being and mental quality of life in sepsis survivors using a median of 2 VR sessions [32, 33]. It is however unknown whether these findings can be extrapolated to a broader ICU population, and if such a modality can be structurally implemented in ICU aftercare, such as in post-ICU follow clinics, where patients are first invited at 3 months after hospital discharge [34]. In the current trial, we therefore aim to extend our previous findings and examine the effect of ICU-VR 3 months after hospital discharge on psychological well-being and quality of life in patients treated for COVID-19.

## Objectives {7}

The primary objective is to examine whether COVID-19 specific ICU-VR, 3 months after hospital discharge, improves psychological well-being and quality of life. Secondary objectives are, firstly, to examine the intra-group changes in psychological well-being and quality of life and the inter-group differences in psychological well-being and quality of life during follow-up, up to 12 months after hospital discharge, and secondly to examine patients’ satisfaction with and rating of ICU care and aftercare and patients’ perspectives on ICU-VR.

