## Trial design {8}

A multicentre, open-label, randomized controlled, superiority, crossover trial.

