## Interventions

### Explanation for the choice of comparators {6b}

In this study, patients in both randomization groups (i.e. the early and late ICU-VR group) will receive the intervention, either 3 or 6 months after hospital discharge. As such, no comparator is used.

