### Intervention description {11a}

Both groups will receive the ICU-VR intervention during the study period, 3 (early) and 6 (late) months after hospital discharge. ICU-VR (duration: ±14 min) comprises several modules explaining the aspects of ICU treatment that are known to be the most frightening [24, 35]. The content was previously determined by a multidisciplinary team and has been demonstrated to be safe [32, 33]. For COVID-19 ICU survivors, we adapted the latter module by adding additional COVID-19 specific aspects of ICU treatment (i.e. mechanical ventilation in prone position, tracheostomy and isolation measures). In addition, information regarding SARS-CoV-2 and COVID-19 was added, and the voice-over was changed accordingly. Real ICU nurses and physicians were used to re-enact a typical day/treatment for a mock patient undergoing ICU treatment for COVID-19.

ICU-VR is hospital-specific, to expose patients to the actual environment where they were treated. As such, each hospital has its unique ICU-VR. An overview of the ICU-VR intervention of the Erasmus MC is depicted in Fig. 1, and the film script can be found in Additional file 1 (translated from Dutch to English). The intervention will be watched via head-mounted display (HMD-)VR glasses (Oculus Go, Irvine, CA, www.oculus.com/go), and patients will be allowed to move their head freely as to experience all aspects of the virtual environment.

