## Statistical methods

### Statistical methods for primary and secondary outcomes {20a}

Baseline demographics and treatment-related characteristics will be quantified using descriptive statistics. Continuous variables will be presented as medians (95% range). Categorical variables will be presented as absolute numbers and relative frequencies.

Differences between study groups in continuous variables, such as the IES-R sum score, the HADS anxiety and depression scores, the RAND-36 subscales and the EQ-5D utility score, at several follow-up time points will be analysed using a mixed effect linear regression model with a random intercept for each study site. Patients will also be categorized based on clinically meaningful cut-offs for the IES-R sum score and the HADS anxiety and depression scores. An IES-R sum score ≥ 24 will be considered as clinically relevant PTSD; a HADS anxiety or depression score > 8 will be considered as clinically relevant anxiety or clinically relevant depression, respectively [36, 41, 46]. Differences in categorical variables between study groups at several follow-up time points will be analysed using a mixed effect logistic regression model with a random effect for each site. Differences in continuous or categorical variables throughout follow-up will be analysed using a mixed effect linear or logistic regression model with an interaction variable of time*randomization and a random intercept and/or slope for each individual and each study site as appropriate.

To determine whether there are time-specific windows of opportunity (3 or 6 months after hospital discharge) for the effect of ICU-VR, we will analyse psychological impairments and quality of life 1 month (4 and 7 months after hospital discharge in the early and late intervention groups, respectively), 3 months (6 and 9 months after hospital discharge in the early and late intervention groups, respectively) and 6 months after receiving ICU-VR (nine and 12 months after hospital discharge in the early and late intervention groups, respectively) using mixed effect linear/logistic regression models with a random intercept for each site and an interaction variable time*randomization.

All data will be gathered using Castor EDC. All analyses will be performed using SPSS (version 24.0; SPSS Inc., Chicago, IL) and R for Statistics (R Foundation for Statistical Computing, Vienna, Austria, 2015). A *P* value ≤ 0.05 will be considered statistically significant.

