Exposure therapy using VR to treat non-ICU-related anxiety and PTSD has demonstrated to be equally effective as in vivo exposure, the gold standard for PTSD and anxiety treatment, and was preferred by patients [28, 49, 50]. Previously, we demonstrated that a sepsis specific ICU-VR intervention improved psychological recovery and mental quality of life in sepsis survivors after ICU treatment [33]. The ideal timing of ICU-VR remains however unknown and the question remains whether such a novel modality can be structurally implemented in routine ICU aftercare, such as in post-ICU follow-up clinics, and whether ICU-VR could be applied for recovery in other illnesses. Most ICU follow-up initiatives are organized 3 months after discharge; consequently, implementation at this time-point would result in a much more feasible implementation of the intervention in existing ICU aftercare programmes [51]. We therefore wanted to determine its effect 3 months after hospital discharge. In a previous study, ICU-VR was applied in a very early stadium, i.e. 8 days after ICU discharge, which could limit its implementation because this would increase work-load [33]. Because the burden for critical care services has risen exponentially in response to the COVID-19 pandemic, we were especially interested to assess its effect as part of our regional ICU aftercare and its effect in COVID-19 patients. Additionally, it is unknown whether a later intervention could also relieve stress and improve quality of life. We therefore also studied the effect of ICU-VR exposure 6 months post-discharge in the control group.

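### The design is a one-way delayed-intervention trial, not a crossover: after month 6 nobody is untreated, so within-arm changes and the late ICU-VR effect are mixed with natural recovery, and no stated analysis isolates the late effect

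*Protocol article*

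**What the plan says.** Trial design {8} calls the study "A multicentre, open-label, randomized controlled, superiority, crossover trial". Explanation for the choice of comparators {6b} notes that both groups receive the intervention and concludes: "As such, no comparator is used". Intervention description {11a} gives the sequence: "Both groups will receive the ICU-VR intervention during the study period, 3 (early) and 6 (late) months after hospital discharge". Participant timeline {13} adds that the month-6 questionnaire is sent before the late arm's ICU-VR visit.

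The first secondary objective in Objectives {7} is "to examine the intra-group changes in psychological well-being and quality of life", paired with between-group differences, up to 12 months. Outcomes {12} repeats it. The Discussion adds a further aim: "We therefore also studied the effect of ICU-VR exposure 6 months post-discharge in the control group".

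Statistical methods {20a} plans between-group comparisons at each time point and, across follow-up, mixed models with a time-by-randomisation interaction. A separate timing-window analysis aligns the arms on time since ICU-VR, starting with "4 and 7 months after hospital discharge in the early and late intervention groups, respectively", and is fitted "using mixed effect linear/logistic regression models with a random intercept for each site and an interaction variable time*randomization". The section ends with a general significance threshold of 0.05.

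**The concern.** A crossover separates treatment from period because some patients take the conditions in the opposite order. Here, after randomisation, the only later move is the late arm's, from untreated to treated; nobody goes from ICU-VR to no ICU-VR. The label therefore promises a protection that the schedule cannot give. The comparator section and the Discussion also disagree on whether there is a control group at all.

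The practical risk lies in the secondary results. ICU survivors may improve over months without ICU-VR. If the late arm improves after month 6, nothing in the article says how much of that may be credited to ICU-VR, and the Limitations section does not raise the question. A before-after improvement could then be read as evidence that ICU-VR still works when given at 6 months.

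**Working it through.** **Step 1. Who is untreated, and when (Participant timeline {13}, Intervention description {11a}).**

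| Interval after discharge | Early arm | Late arm | Untreated concurrent control? |
|---|---|---|---|
| Month 3 to 6 | ICU-VR at month 3 | no ICU-VR yet | yes, the late arm |
| Month 6 to 12 | already treated | ICU-VR at month 6 | none |

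The primary outcome window (Outcomes {12}, up to 6 months) lies wholly in the first row.

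**Step 2. What each contrast estimates.** For month 6 to 7, let g be the natural change, v the effect of late ICU-VR, and e any further change in the early arm's ICU-VR effect over that month.

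- Late arm, before-after: g + v. This equals v only if g = 0.
- Early arm, before-after: g + e.
- Difference between arms: (g + v) − (g + e) = v − e. Natural recovery cancels in expectation because the arms were randomised. The result equals v if e = 0, that is, if the early arm's effect is stable by month 6.
- Timing-window comparison (early at month 4, late at month 7): the late arm is three months further from discharge, so recovery over those months does not cancel. It addresses timing but does not isolate v.

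**Step 3. Number of completers.** Sample size {14} gives 80 patients with 20% loss: 80 × 0.8 / 2 = 32 per arm. The 80 itself can be reproduced with d = 0.77, two-sided alpha 0.05, power 0.80 and a Wilcoxon-Mann-Whitney test at its minimum relative efficiency (0.864): 32 per arm, 64 / 0.8 = 80. The article does not name that test; it is inferred from the remark in Limitations that no distribution was assumed.

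**Step 4. Illustration of a within-arm test with no ICU-VR effect.** Assumed, because the article gives neither: natural improvement δ in SD units, and within-patient correlation r of 0.5 to 0.7. The SD of change is √(2(1 − r)), which is 1.00 at r = 0.5 and 0.775 at r = 0.7. The noncentrality is δ√32 / √(2(1 − r)). Two-sided paired t test, 31 degrees of freedom:

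| δ (SD) | noncentrality (r = 0.5; 0.7) | proportion significant (r = 0.5; 0.7) |
|---|---|---|
| 0 | 0; 0 | 5%; 5% |
| 0.1 | 0.57; 0.73 | 9%; 11% |
| 0.2 | 1.13; 1.46 | 20%; 29% |
| 0.3 | 1.70; 2.19 | 38%; 57% |

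In simulation (5,000 trials per setting, δ of 0.2 or 0.3, r of 0.6 or 0.7), the between-arm test of the same change rejected in 4-5% of trials.

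**Step 5. Precision of the between-arm contrast.** Standard error = √(2(1 − r)) × √(2/32) = 0.25 SD at r = 0.5 and 0.19 SD at r = 0.7. This is √2 times the within-arm standard error (1/√32 = 0.18 and 0.775/√32 = 0.14).

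**The case against.** The strongest reply is that the plan names no within-arm test. The inference specified in Statistical methods {20a} is between arms, the 0.05 threshold is a general closing statement, and the objective pairs within-group change with between-group differences without a causal verb. The time-by-randomisation model is already planned, months 6 and 7 are both scheduled visits, and no crossover or carry-over model rests on the label. All of this stands. It makes the percentages above conditional, and it means most of the remedy needs only to be designated. It does not remove the Discussion's stated aim for late ICU-VR, for which no contrast is identified, nor the conflict between the comparator section and the Discussion.

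Three stronger readings are tempting and are not supported:

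- A reader might infer from the comparator section that the primary comparison is uncontrolled. It is not: the late arm is untreated through the month-6 questionnaire, and the early arm's change from month 3 to 6 has a randomised comparator.
- A reader might add regression to the mean as a second source of bias. Eligibility {10} sets no symptom threshold, and late ICU-VR is given whatever the month-6 score, so group means were not selected on extreme values. Natural recovery is the mechanism that remains.
- A reader might say that a significant within-arm improvement is to be expected even without an effect. That depends on the assumed recovery: at 0.1 SD the rate is about 10%, and the proposed contrast spans only one month.

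**Conclusion.** The point holds for the secondary results and for the description of the design. The crossover label is wrong, the no-comparator statement contradicts the control group of the Discussion, and after month 6 neither within-arm changes nor a before-after effect of late ICU-VR can be separated from natural recovery. No stated analysis is assigned to isolate the late effect. The primary early-versus-late question to month 6 is not affected.

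The structural conclusion needs no numerical assumption. Its size does: the false-attribution rates run from about 10% to 57% for recovery of 0.1 to 0.3 SD, assume 32 completers and correlations of 0.5 to 0.7, and apply only if within-arm changes are tested and credited to ICU-VR. The correction should be made, because it gives a less biased estimate from data already scheduled.

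**What to change.** 1. In Trial design {8}, describe a parallel-group trial with a delayed-intervention control. In the comparator section, state that the comparator through the month-6 questionnaire is usual aftercare without ICU-VR, and bring the Discussion into line.
2. From the planned time-by-randomisation model, designate the between-arm difference in change from month 6 to month 7 as the estimate of the late ICU-VR effect. State that it assumes the early arm's effect is stable by month 6. If that effect is still growing, the contrast understates the late effect; if it is waning, the contrast overstates it.
3. Report within-arm changes as estimates with confidence intervals, without attributing them to ICU-VR. Say that the timing-window comparison is confounded with time since discharge.

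The cost is wording and one contrast, with no new visits or patients. The price is precision: with a standard error of 0.19 to 0.25 SD, the 95% interval is roughly ±0.39 to ±0.50 SD (t of about 2.0 on 62 degrees of freedom, unadjusted), so only a fairly large late effect could be shown. The changes should be recorded before the allocation codes are linked to the arms.

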## Trial design {8}

A multicentre, open-label, randomized controlled, superiority, crossover trial.

## Methods: participants, interventions and outcomes

### Study setting {9}

This multicentre, randomized controlled, open-label trial will be conducted in the mixed-medical ICUs of four hospitals in Rotterdam, the Netherlands: one university hospital providing tertiary care (Erasmus MC) and three teaching hospitals providing secondary care (Franciscus Gasthuis & Vlietland Hospital, Ikazia Hospital and Maasstad Hospital).

### Eligibility criteria {10}

We aim to include patients older than 18 years of age with COVID-19, determined by a positive SARS-CoV-2 PCR, necessitating ICU care. Patients discharged from the hospital between March 29 and September 30, 2020, and who are able to understand the Dutch language are eligible for inclusion. Patients will be excluded when they suffer from active, established psychiatric disease, for instance personality disorders or schizophrenia; are admitted with a history or a primary neurological impairment necessitating ICU treatment; have no formal home address; or are enrolled in other interventional studies that could confound the primary endpoint.

### Who will take informed consent? {26a}

Patients admitted for COVID-19 to the ICU of the participating hospitals will be invited to a post-COVID-19 outpatient clinic 3 months after hospital discharge as part of the regional standard of care. All patients will receive an information letter and will be contacted by telephone by one of the members of the research team to discuss participation 1 month prior to this visit. During the outpatient clinic visit, informed consent will be obtained by the principal investigator of the study site, or by one of the other members of the research team if the principal investigator is unavailable.

### Additional consent provisions for collection and use of participant data and biological specimens {26b}

Not applicable, no additional participant data or biological specimens were obtained.

## Interventions

### Explanation for the choice of comparators {6b}

In this study, patients in both randomization groups (i.e. the early and late ICU-VR group) will receive the intervention, either 3 or 6 months after hospital discharge. As such, no comparator is used.

